#### Aim 2a: Data Analysis

To test our hypothesis that coprescribed medications will be associated with an increased risk of opioid side effects (eg, benzodiazepines and somnolence), we will include only study patient participants who are prescribed opioids. Linear mixed-effects models will be used to assess the relationships between selected risk factors and the corresponding suspected opioid side effects. Each side effect is scored on the respective weekly or monthly assessments. Analyses will be conducted to examine the relationship between coprescribed medications and each of the respective opioid side effects (constipation, nausea, dry mouth, and somnolence) as well as targeted relationships specifically of interest for individual exposures or side effects combinations, including (1) coprescription of other constipating medications and constipation, (2) coprescription of other constipating medications and nausea, (3) coprescription of anticholinergic medications and dry mouth, and (4) coprescription of benzodiazepines with somnolence. We will also examine the association between which opioid is prescribed (ie, morphine vs oxycodone) and each of the same respective opioid side effects (constipation, nausea, dry mouth, and somnolence). The use of linear mixed-effects models will provide estimates of the effect of each risk factor of interest on each of the respective side effects while also allowing the inclusion of longitudinal measurements from patient participants.

#### Power Calculation for Aim 2a

With an overall sample size of 630, we anticipate approximately 50% (315/630) of the study sample to be prescribed opioids, leaving 315 patient participants available for the analyses pertinent to this hypothesis. We examined a range of scenarios allowing anywhere from 10% to 30% of the eligible participants to have each exposure, performing power analyses to detect a 0.5-point difference in means for each side effect on the 1-5 scale (assuming a SD of 1 point). Power is about 65% if the exposure is rare (10% of patients prescribed opioids) but increases to 87% if the exposure is present in 20% of patients prescribed opioids and 93% if exposure is present in 30% of patients prescribed opioids. Again, we account for up to 40% attrition during the study. Note that patient participants will contribute data until they drop out, and this data will be included in the analysis.

#### Aim 2: Data Analysis to Test Hypothesis 2b

To test our hypothesis that younger age, history of substance use disorder, and history of mood disorders will be associated with a greater risk of opioid misuse and use disorder, we will perform multivariable Cox regression analyses to assess the respective risk factors of interest. We will use a single prespecified model that includes age, history of substance use disorder, and history of mood disorders using baseline PRO data and chart review.

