## Methods

### Study Design

This is a multicenter, prospective cohort study that aims to enroll 630 patients with advanced cancer, 20 care partners, and 20 clinicians (670 total participants). The data collection is underway at 4 clinical sites. Site selection considered geographic diversity (Northeast, mid-Atlantic, West, and Southeast), the balance of urban versus rural patients, sufficient patient volume to reach the enrollment goal, and the ability to recruit based on previous success in cancer studies. Given well-established health disparities in cancer pain and its treatment, we selected sites that demonstrated a track record of successful recruitment of Black and Hispanic patient participants [31]. None of the chosen sites have opioid stewardship committees or programs, which could have the unintended consequence of limiting opioid prescribing [32]. Additionally, we conducted a comprehensive review of state opioid laws in preparation for the study [33], with most states specifying blanket cancer exemption for any opioid limitation, such as dose or limited day supply.

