### Analytic Plan

#### Aim 1: Data Analysis

This analysis will draw from all patient participants, regardless of whether they are prescribed opioids, so we can compare those who are with those who are not prescribed opioids. We will estimate differences in pain severity and interference between patients treated with opioids versus patients not treated with opioids using linear mixed-effects models, which will allow us to (1) account for repeated measures over time for each patient and (2) adjust for potential confounders. In the linear mixed-effects models, the dependent variables will be based on the PEG: pain severity (first question is a continuous 0-10 value) and pain interference (mean of 3 PEG items) at each time point. Current opioid prescription, baseline pain severity or interference, and other confounders (ie, factors statistically associated with the exposure and outcome) will be included as fixed effects, while the subject will be included as a random effect.

#### Power Calculation for Aim 1

Power calculations were performed by simulation to allow a range of parameters to vary in all scenarios. Unlike a randomized trial, in this study we will not have control over the ratio of patients allocated to the 2 comparison groups (eg, there will not be precisely a 1:1 ratio of patients prescribed opioids vs patients not prescribed opioids for comparison). Scenarios were considered where the proportion of patients prescribed opioids was allowed to vary from 30% up to 70%, all assuming a mean baseline PEG of 6 in the patients not prescribed opioids, a reduction in the PEG of 1 point for patients that are prescribed opioids, and a common standard deviation in PEG scores of 2 points [51]. All scenarios considered had at least 90% power to detect a difference of 1 point between groups with a total sample size of 630 patients (allowing for 30%-70% of the population to be prescribe opioids, meaning that with a range of 189 up to 441 patients prescribed opioids during the study period, there is ample power to detect differences between groups). All scenarios had at least 99% power to detect a 2-point difference on the PEG. We acknowledge that up to 40% of patients may drop out during the study due to the morbidity and mortality of patients in palliative care [58]. Data up until the point of attrition will be included in the analysis, and this has also been accounted for in our calculations.

#### Missing Data for Aim 1

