## Discussion

This paper presents the study protocol for the benefits, harms, and stakeholder perspectives regarding opioid therapy for pain in individuals with metastatic cancers .The study also uses PRO measures, qualitative data collection, and repeated assessments to ascertain how decision-making differs throughout the cancer trajectory, including at the end of life. The protocol is innovative because it addresses the research gap on the benefits and harms of opioids in metastatic cancer in a novel way. This includes our prospective design in patients recently diagnosed with advanced cancer, the collection of data from multiple perspectives (patients, clinicians, and care partners), and the inclusion of a well-known decision-making framework that can facilitate the design of future interventions.

There are several potential challenges or limitations to the research protocol. The first is likely challenges of retention and recruitment that are expected in longitudinal studies, especially in individuals with cancer and serious illnesses. Second, there is a potential for low enrollment or a high rate of missing data due to death, illness, dropout, or participant burden. We have attempted to account for these anticipated issues by having backup recruitment sites and conservative sample size estimates. Third, opioid prescribing is an evolving area of clinical practice and subject to federal and state oversight. It is possible that local and state regulations or institutional policies will change during the study period, resulting in a decrease in opioid prescribing and recruitment issues. Last, prospective investigation of adverse effects such as overdose or opioid-related mortality may be difficult to capture because these events are relatively rare.

At the end of the study, we anticipate the development of a comprehensive evidence base on opioid therapy in individuals with advanced cancer, guided by the BDR framework. The information gained from this study will be used to guide interventions to facilitate opioid decisions among patients, clinicians, and care partners. Given the limited evidence base about opioid therapy in people with cancer, we envision this study will have significant real-world implications for cancer-related pain management and opioid-related clinical decision-making.

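### The Aim 2b Cox model is fixed with no site term or stratum, so site differences in case mix or charting can bias its hazard ratios; site should also be prespecified in Aim 1

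*Protocol article*

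**What the plan says.** Under the data analysis for Hypothesis 2b, the protocol article plans multivariable Cox regression for opioid misuse and use disorder and fixes its content: "We will use a single prespecified model that includes age, history of substance use disorder, and history of mood disorders". The histories come from baseline patient reports and chart review. No site covariate, stratum, frailty or cluster term is named, and nothing provides for further adjustment.

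Under Study Design, "The data collection is underway at 4 clinical sites", and the sites were picked partly for contrast: "Site selection considered geographic diversity (Northeast, mid-Atlantic, West, and Southeast), the balance of urban versus rural patients". Table 1 lists quarterly chart review among the sources for substance use, misuse and overdose. The section on missing data for Aim 2 counts a complication as an event when it is known, and otherwise takes it not to have occurred while the patient is observed.

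Aim 1 is specified differently. Its fixed effects are given as "Current opioid prescription, baseline pain severity or interference, and other confounders (ie, factors statistically associated with the exposure and outcome"), "while the subject will be included as a random effect". Site is not named there, but the confounder clause leaves room for it.

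**The concern.** In a multicenter cohort, site can be related both to who carries a risk factor on paper and to how often the outcome is recorded. Aim 2b is exposed to this in two ways.

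- **Case mix.** Sites chosen to differ in region and urban/rural balance may differ in the prevalence of substance use or mood disorder history and in the underlying risk of misuse.
- **Ascertainment.** A site that charts more thoroughly may record more histories and more events. Because unrecorded complications become non-events, thinner documentation elsewhere passes directly into the outcome. Both errors then run in the same direction and push the hazard ratio away from 1.

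At stake are the hazard ratios by which the study would identify patients at greater risk of misuse or use disorder. For Aim 1 the issue is narrower: whether a known design factor is adjusted for depends on a test of association in the data.

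**Working it through.** **1. The plan's own figure.** Under the power calculation for Aim 2b, 0.50 × 630 = 315 patients, which reproduces. At a 10% rate of opioid use disorder, 315 × 0.10 = 31.5 events, or 31.5 / 5 = 6.3 per candidate for the five candidate predictors mentioned there. The article states no hazard ratio, power or events-per-variable rule, so its judgement that this is sufficient cannot be reproduced. The model section names three predictors. The other two are not identified, so site cannot be assumed to be one of them; as indicators, four sites would need three terms.

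**2. Possible size of the bias.** The article gives no site figures, so every site difference here is an assumption. Take sites of equal size, history prevalence p at each site, recorded event rate h at each site, and no true effect of history within any site. The pooled rate ratio is

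[Σ(p·h) / Σp] ÷ [Σ((1−p)·h) / Σ(1−p)].

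This approximates the hazard ratio from a model without site. It leaves out the adjustment for age and mood disorder, which might absorb part of the site difference.

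| Assumed history prevalence | Highest-to-lowest event rate 1.5 | Highest-to-lowest event rate 3 |
|---|---|---|
| Four sites: 10, 13, 17, 20% | 1.05 | 1.12 |
| Four sites: 5, 12, 18, 25% | 1.09 | 1.24 |
| Two pairs of sites: 10% and 20% | 1.08 | – |
| Two pairs of sites: 5% and 25% | – | 1.42 |

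The four-site rows use event rates rising in equal ratios from lowest to highest. The two-pair extremes work out as follows:

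- 5% and 25%, rate ratio 3: (0.25×3 + 0.05)/0.30 = 2.667; (0.75×3 + 0.95)/1.70 = 1.882; ratio 1.42.
- 10% and 20%, rate ratio 1.5: (0.20×1.5 + 0.10)/0.30 = 1.333; (0.80×1.5 + 0.90)/1.70 = 1.235; ratio 1.08.

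If p or h is the same at every site, the ratio is exactly 1. If they vary in opposite directions, it falls below 1.

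**3. Ways to include site in Aim 2b.**

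| Outcome (rate) | Events | Per term, 3 terms or stratified | Per term, 3 terms + 3 site indicators |
|---|---|---|---|
| Use disorder (10%) | 31.5 | 10.5 | 5.25 |
| Misuse (20%) | 63 | 21 | 10.5 |
| Misuse (30%) | 94.5 | 31.5 | 15.75 |

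Stratification gives each site its own baseline hazard and estimates no extra coefficient. Its price is that only within-site contrasts count. As an approximation, the information lost is the share of the risk factor's variance lying between sites, Var(p) / [p̄(1−p̄)], with p̄ = 0.15 in every row of the first table:

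- 10, 13, 17, 20%: 0.00145 / 0.1275 = 1.1%.
- 5% and 25%: 0.0100 / 0.1275 = 7.8%.

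Standard errors then grow by 1/√(1−0.011) to 1/√(1−0.078), about 0.6% to 4%.

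**4. Cost of naming site in Aim 1.** Inputs are a 1-point difference and SD 2 from the article, and two-sided alpha 0.05, which is assumed. Suppose site explains 2% to 9% of the exposure variance (also assumed). Power then stays at or above 0.989 even at N = 630 × 0.60 = 378, the worst case under 40% attrition. No bias is sized for Aim 1, because a calculation without baseline pain would describe a model the plan does not use.

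**The case against.** The strongest objection is that this is a condensed article, and how center enters a model is routinely left to the analysis plan. That disposes of any complaint about Aim 2a, whose section simply does not list covariates. It does not dispose of Aim 2b, where the article states a single prespecified model, lists its content and leaves no opening. It can be said that listing what a model includes does not rule out more, and that the sizing mentions five candidates; but the other two are unnamed.

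A reader might also infer that Aim 1 ignores site and will report site differences as opioid effects. The text does not support this. Opioid prescription and baseline pain are fixed effects, and other confounders are admitted when associated with exposure and outcome, so site can enter when it matters. Only the reliance on that screen remains open to criticism. Nor should the 30% to 70% opioid share in the Aim 1 power section be read as a spread between sites; it is uncertainty about the whole cohort.

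Some facts limit site differences. "None of the chosen sites have opioid stewardship committees or programs", and the review of state laws ends "with most states specifying blanket cancer exemption for any opioid limitation, such as dose or limited day supply", without saying that any study site lies in a state lacking the exemption. The Discussion's remark, "It is possible that local and state regulations or institutional policies will change during the study period", concerns falling prescribing and recruitment, not confounding. Misuse is also measured by a common patient-reported instrument, and one coordinating team conducts follow-up assessments. Table 1 does not say who reviews charts for misuse. These points make a large bias less likely but do not remove the possibility.

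**Conclusion.** The point holds for Aim 2b. The stated model omits a design factor that may be related to both the recorded histories and the recorded events, and a better analysis is available at little cost. Under the assumed site differences, a true hazard ratio of 1 could appear as about 1.05 to 1.4. The upper end needs a sharp split between two pairs of sites, with prevalence and event rate aligned; smoother gradients give 1.05 to 1.24. The bias is a possibility and not a demonstrated result, and it vanishes if either quantity is constant across sites.

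For Aim 1 only the smaller point stands: site should be fixed in advance and not left to an association screen. Nothing is concluded about Aim 2a.

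**What to change.** - **Aim 2b:** state that the Cox model is stratified by site. This takes one sentence and no extra coefficient, and it is preferable to three indicators given about 31.5 use disorder events. The cost is the small loss of precision shown above.
- **Aim 2b text:** reconcile the three named predictors with the five candidates in the sizing, and name the other two or drop them.
- **Aim 1:** name site as a prespecified fixed effect (three degrees of freedom), whatever the confounder screen shows. Power remains ample.

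The article says study data are segregated by research site, so no new data collection is needed. Follow-up is planned to end by November 2026, so the change can be recorded before the final analysis.

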#### Power Calculation for Aim 2b

With a total sample size of 630 patients recruited in Aim 1, the power calculation for this subaim assumed a scenario where approximately 50% (315/630) of the patients are prescribed opioids, leaving 315 patients available for this aim. We anticipate opioid misuse will occur in 20% to 30% of patients. For a rarer event such as opioid use disorder, which is estimated to occur in approximately 10% of the patients, a sample size of 315 patients will be sufficient to support a model with 5 candidate predictor variables.

#### Missing Data for Aim 2

Unlike Aim 1, missing data should not affect analyses in this aim. The development of opioid-related complications will also be considered an event if it is known to occur and otherwise assumed not to occur during the period patients are under observation.

#### Aim 3: Data Analysis

The purpose of Aim 3 is to identify what patients, care partners, and clinicians already know and how they make opioid-related decisions to develop the lay model of the BDR. To determine decisional influences, the BDR framework uses the “mental models approach” to elicit these views [59]. To create the BDR framework lay model, we will structure the patient and care partner interviews by focusing on (1) what they already know about opioids, (2) how they make decisions, (3) examining whether this is consistent with or contrary to the normative model of evaluating risks and harms, and (4) how they think decisions around opioid use should ideally be made. The interviews begin with general questions and then become more specific, asking about each topic from the expert model. We will structure the clinician interviews by focusing on (1) their assessment of the patient’s pain; (2) approaches to best treating it, including opioids; and (3) their decision-making around opioid prescribing. We will also evaluate whether different patient, care partner, and clinician perspectives are consistent with or contrary to one another.

For the semistructured interviews (40 participants with metastatic cancer from our larger cohort, 20 who are prescribed opioids at the time of enrollment, and 20 who are not), we aim to understand perspectives on deciding to initiate or continue opioid therapy or not. This sample size is based on evidence that suggests thematic saturation is achieved at 8-16 interviews; since we expect up to 40% attrition, this approach will ensure we have at least 20 participants [60]. We will purposively sample [61] to ensure diversity on race, site, and baseline PEG value; we will also recruit some individuals who have a history of a substance use disorder and are therefore at particularly high risk for negative consequences when prescribed opioids.

Similarly, we will recruit patient participants’ care partners and clinicians. We will aim for at least 10 people who have care partners who consent to the group prescribed opioids at enrollment and 10 care partners of patient participants who have been prescribed opioids at enrollment. This approach will ensure that we have enough care partners to provide adequate perspective but not severely bias our sample by only allowing the enrollment of individuals who have care partners willing and able to enroll in this study. As described above, we will also purposefully sample 25% of patient participants who do not have care partners so that these perspectives are represented. Interviewing patients and their care partners s and clinicians will allow for triangulation of findings. Additionally, following patients, care partners, and clinicians longitudinally will allow for a detailed understanding of how decision-making changes over the course of metastatic cancer, allow participants to reflect on what they would have liked to know earlier based on what they know now, and provide real-time data on actual decisions (eg, initiation or discontinuation of opioids) on which participants can be asked to comment. Given the challenges inherent in engaging clinicians, we will aim for 15-minute focused interviews.

Trained qualitative researchers will collect and analyze the qualitative data. Interviews will be conducted remotely (through phone or Zoom [Zoom Video Communications], according to the interviewee’s preference), and interview recordings will be transcribed verbatim (with details that might identify the interviewee redacted). Coding the data will require a hybrid deductive-inductive approach. A prespecified set of codes will be identified from the normative model. The presence and absence of these codes (eg, the accuracy of knowledge about the relationship between opioids and addiction) will be used to document the consistency between the normative model and stakeholder perspectives. In addition, we will take an inductive analytical approach to identify emergent values and beliefs that are not present in the normative models. Codes will be developed through open coding of the transcripts to determine topics and themes that emerged in the interview transcripts with input on topics or themes that the study team anticipates being relevant, resulting in simultaneously inductive and deductive development of the codebook. A draft codebook including detailed code definitions will be discussed with the study team to ensure that codes reflect both the data as they are emerging as well as relevant topical themes that are important to the team. Codes will be thoroughly checked to determine that definitions are distinct enough to reduce ambiguity in the coding process.

About 25% of the transcripts will be coded by 2 independent, trained qualitative coders to ensure quality and consistency in coding. Coding will then be compared for the purposes of calculating Cohen kappa inter-coder reliability scores [62]. Any coding discrepancies identified during this comparison will be adjudicated by the coders until full agreement on coding is achieved. The finalized coding on these transcripts will be recorded in a single ATLAS.ti file, following which the primary coder will complete the coding of the remaining transcripts according to the codebook and through the adjudication process and discussion by the study team with content and methodologic expertise. This process allows for consistency and quality across transcripts. Once coding is complete and uploaded to ATLAS.ti with quotes associated with codes, we will thematically analyze and determine the relative frequencies of various codes and the most salient themes. The resulting thematic analysis will be discussed with the entire investigator team to use the findings to build lay models of patient, care partner, or clinician decision-making around opioid use for patients with metastatic cancer.

